### Statistical Analysis

#### Data Analysis

In the statistical analysis, quantitative measures will be summarized with means, SDs, and quantiles, and categorical measures, including the presence of trigger points (trigger points vs healthy tissue), will be summarized with counts and percentages. Data will be described for 3 calf muscles (medial gastrocnemius, lateral gastrocnemius, and medial soleus) and 2 foot muscles (abductor hallucis and flexor digitorum brevis).

The primary study aim is to examine the diagnostic performance of 20 candidate biomarkers (biomechanical, biochemical, and structural) in distinguishing between tissue with and without myofascial pain. Performance will be quantified with the area under the receiver operating characteristic curve (ROC AUC), pooled over the 5 muscle groups assessed on each participant for imaged metrics and trigger points. Five-fold cross-validation will be used to estimate predictive performance, and bootstrap resampling applied to obtain 95% CIs. Participants will be treated as the sampling units in cluster cross-validation and bootstrap sampling algorithms to account for repeated muscle measurements in each participant. To identify the most promising biomarkers and account for multiple comparisons, false discovery rates will be computed with the method of Benjamini and Hochberg to rank the biomarkers in order of diagnostic performance [73]. Up to 5 top-performing biomarkers will be selected to constitute a single biosignature to achieve a target AUC >0.7, sensitivity >60%, and specificity >60%.

In an exploratory aim, composite biosignatures will be developed from imaging biomarkers, patient demographics, and psychological factors. Traditional statistical and machine learning techniques will be used. Logistic regression models, fit with the method of general estimating equations, will be used specifically to test for interactions between imaging biomarkers and sex. Composite models will be built from the full set of predictors using stepwise variable selection as well as the machine learning methods of Lasso, gradient boosting, and random forests. The latter 2 methods have the distinction of performing automated encoding of nonlinear and interaction effects. ROC AUC will be estimated as the measure of diagnostic performance for each model, as described for the primary aim. In addition, variable importance will be reported to quantify the relative contributions of predictor variables, and partial dependence plots will be constructed to show the functional forms of their effects.

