**Objective:**

This protocol describes the development of a diagnostic imaging biosignature of myofascial pain using both ultrasound and magnetic resonance imaging to differentiate individuals with plantar heel pain from those with other kinds of foot pain and matched pain-free controls. The study will also explore whether diagnostic accuracy is enhanced by creating a composite biosignature that includes psychological factors.

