Imaging is a powerful, yet underused, diagnostic tool that can be used to identify muscles with trigger points [15]. Ultrasound and magnetic resonance imaging (MRI) are both commonly used clinically to evaluate soft tissues [16-18]. Ultrasound is a noninvasive imaging technique with minimal contraindications that provides real-time assessments of soft tissue, including muscles and fascia [19]. In particular, ultrasound shear wave elastography (SWE) demonstrates high diagnostic accuracy in capturing abnormal biomechanical properties of myofascial tissue [15]. MRI is often regarded as the gold standard for evaluating soft tissues due to its ability to provide superior contrast, high resolution, and multiplanar images [18]. Previous studies have shown promise using T1 signal intensity and T2 mapping to detect structural alterations in trapezius muscles in women with migraines [20-22]. To build on previous foundational work, further research is needed to examine the diagnostic capabilities of both ultrasound and MRI within the same sample and to expand imaging approaches for identifying trigger points in the foot and ankle.

The primary aim of this proposed study is to develop a diagnostic imaging biosignature of myofascial pain to differentiate individuals with plantar heel pain from those with other kinds of foot pain (specifically insertional Achilles tendinopathy) and from matched pain-free controls. We hypothesize that a diagnostic biosignature, which uses both advanced ultrasound and MRI to quantify biochemical (muscle and fascia T1ρ), biomechanical (muscle SWE and fascia strain), and structural (muscle fat fraction and fascia thickness) tissue properties, will more accurately identify myofascial pain in the foot and ankle than a single imaging biomarker alone. We will also explore the potential of composite biosignatures that combine multiple imaging biomarkers with psychological factors, such as kinesiophobia, to provide a more comprehensive assessment. The development of a diagnostic biosignature may provide novel mechanistic insights into myofascial pain and offer a framework to facilitate the diagnosis of myofascial pain contributing to plantar heel pain.

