The physical therapist will palpate within the 5 zones to determine if a trigger point is present and mark the tautest band using a waterproof marker in a cross shape in each zone. This approach allows for the same locations to be assessed with ultrasound imaging and MRI. Trigger point identification will follow the gold standard diagnostic criteria established by Simons [54], who defines a trigger point as a taut band of skeletal muscle that is tender to palpation. The physical therapist will apply constant pressure with palpation for 5 seconds on the most tender taut band in each of the 5 zones, with a 20-second rest between each spot. Participants will be asked whether the pressure reproduces the same heel pain [54] and whether the pain is felt locally at the site of palpation or referred to another area [10] at each site. For comparison of imaging outcomes between trigger points and healthy tissue, at least 1 of the 5 marks will indicate healthy tissue using the same cross shape. Imaging researchers will remain blinded to the trigger point versus healthy tissue identification to ensure unbiased image acquisition.

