## Discussion

### Principal Findings

This study is designed to develop a diagnostic imaging biosignature for myofascial pain that differentiates individuals with plantar heel pain from those with other foot pain, such as insertional Achilles tendinopathy, and from pain-free controls. We anticipate that combining imaging and psychosocial measures will improve diagnostic accuracy and provide a more comprehensive understanding of myofascial pain.

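### The primary aim is stated in two ways: the planned analysis classifies muscle sites, and the part about telling plantar heel pain from the two control groups has no described analysis

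*Protocol article*

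**What the plan says.** Three places in the protocol article put the aim at the level of the person, with diagnosis group as the label:

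- Abstract, Objective: the biosignature is "to differentiate individuals with plantar heel pain from those with other kinds of foot pain and matched pain-free controls".
- Introduction, in the sentence that names the primary aim: "to differentiate individuals with plantar heel pain from those with other kinds of foot pain (specifically insertional Achilles tendinopathy) and from matched pain-free controls".
- Discussion, Principal Findings: a biosignature that "differentiates individuals with plantar heel pain from those with other foot pain, such as insertional Achilles tendinopathy, and from pain-free controls".

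Data Analysis also names a primary study aim, but for a different unit and label. There the 20 candidate biomarkers are judged on their performance "in distinguishing between tissue with and without myofascial pain". The AUC is "pooled over the 5 muscle groups assessed on each participant for imaged metrics and trigger points", and the tissue label is given as "the presence of trigger points (trigger points vs healthy tissue". Participants are the sampling units for cross-validation and bootstrap, but only "to account for repeated muscle measurements in each participant".

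The exploratory composite models take their AUC from the primary aim and name no group outcome. Sample Size gives a 95% half-width of 0.10 at an AUC of 0.70, from 5 measurements per participant, an intraclass correlation of 0.5 and an active trigger point prevalence of 36% in plantar heel pain.

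**The concern.** The two statements define different estimands. One asks whether a person has plantar heel pain rather than Achilles tendinopathy or no pain. The other asks whether a marked spot of muscle is a trigger point. Both are called the primary aim, and only the second has an analysis and a precision statement.

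What is at stake is the conclusion. If the biosignature reaches the target AUC on sites, the article's own wording of the aim invites the report that it distinguishes plantar heel pain from other foot pain and from pain-free controls. The site-level result would not show that. Nor would a failure on sites show that the groups cannot be told apart.

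**Working it through.** **1. What the plan's own precision figure refers to.** Inputs from Sample Size: 100 participants with 5 sites each (500 sites), intraclass correlation 0.5, AUC 0.70, 36% positive sites in plantar heel pain (90 of 250). The prevalence in the control groups is not given, so I varied it from 0% to 36%.

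Design effect: 1 + (5 − 1) × 0.5 = 3. Site counts are divided by 3.

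Hanley-McNeil variance: [A(1−A) + (n1−1)(Q1−A²) + (n0−1)(Q2−A²)] / (n1·n0), with Q1 = A/(2−A) and Q2 = 2A²/(1+A). At A = 0.70: A(1−A) = 0.21, Q1−A² = 0.0485, Q2−A² = 0.0865. The half-width is 1.96 × SE.

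| Control prevalence | Positive sites of 500 | Half-width |
|---|---|---|
| 0% | 90 | 0.112 |
| 11% | 117.5 | 0.100 |
| 18% | 135 | 0.095 |
| 36% | 180 | 0.086 |

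The stated 0.10 is therefore attainable as a clustered site-level figure. Without the design effect, the half-width over the same range is 0.049 to 0.064.

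**2. Whether the site label can stand in for diagnosis group.**

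- Trigger Point Identification requires that "at least 1 of the 5 marks will indicate healthy tissue using the same cross shape". Every plantar heel pain participant therefore contributes at least one negative site.
- At 36% prevalence, 250 − 90 = 160 of the plantar heel pain sites are negative, or 64%. That is on average 3.2 of 5 sites per person.
- A trigger point is defined by a tender taut band, which does not rule out positive sites in either control group.
- Eligibility assigns people to the pain groups by clinical diagnosis, not by trigger points.

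The label varies within a person and does not coincide with group, so a site-level AUC gives neither sensitivity nor specificity for plantar heel pain against either control group.

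**3. Precision of the comparisons named in the aim.** One score per participant, assumed AUC 0.70, same formula:

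- 50 v 25 (either control group): (0.21 + 49 × 0.0485 + 24 × 0.0865) / 1250 = 4.660 / 1250 = 0.00373; SE 0.061; half-width 0.120.
- 50 v 50 (pooled controls): (0.21 + 49 × 0.0485 + 49 × 0.0865) / 2500 = 6.822 / 2500 = 0.00273; SE 0.052; half-width 0.102.

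The Obuchowski variance, as a check, gives 0.127 and 0.106. That the pooled result rounds to 0.10 is coincidence: the inputs in Sample Size (sites per person, intraclass correlation, trigger point prevalence) play no part in a participant-level calculation.

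**The case against.** The best defence is that the design is coherent at tissue level. What is to be developed is a biosignature of myofascial pain, and the group clause can be read as describing its use. The Introduction seeks an imaging biomarker for trigger points, and its hypothesis is that the combined biosignature identifies myofascial pain better than a single biomarker. The marking procedure is set up to compare trigger points with healthy tissue. All of this stands, and it limits the point in three ways:

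- A reader might infer that the whole primary aim goes unanswered. The documents do not support that. The tissue-level aim and the hypothesis are addressed; only the group-differentiation part is not.
- A reader might infer that the control groups are recruited for nothing. Data Analysis excludes no group, so their sites enter the pooled AUC, and Sample Size ties the 50/25/25 split to that AUC.
- A reader might infer that the 0.10 is wrong. It is a site-level figure, and it is attainable as one.

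It can also be said that a condensed article may leave group contrasts to an analysis plan that is not shown. Their absence alone would indeed be no finding. But the article itself fixes two primary aims with different units and labels, and a plan that followed Data Analysis would carry the mismatch forward.

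Finally, any rule that turns five sites into one score is a choice, and a score with fascia measures could separate heel-pain patients through fascia changes without detecting myofascial pain. That objection also stands, and it shapes the fix.

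**Conclusion.** The point holds as an inconsistency between stated aim and planned analysis, confined to the group-differentiation part of the aim. No described analysis uses diagnosis group as an outcome, and a site-level AUC above 0.7 cannot support a claim about groups.

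The two comparisons named in the aim have no stated precision. It would be about ±0.12 for each, and about ±0.10 against pooled controls. These figures assume a participant-level AUC of 0.70, full enrolment, one fixed score per person and the Hanley-McNeil variance. They do not include the added uncertainty from selecting biomarkers among 20 candidates. The site-level check assumes that a simple design effect is adequate and that control prevalence lies between 0% and 36%.

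**What to change.** Keep the site-level AUC as the primary analysis and label it as tissue-level. Add a prespecified participant-level analysis:

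- one rule, fixed before the data are analysed, for aggregating the biosignature over the 5 sites;
- separate AUCs, with participant-bootstrap confidence intervals, for plantar heel pain versus insertional Achilles tendinopathy and versus pain-free controls;
- any score that includes fascia measures reported separately;
- its own precision statement: about ±0.12 at an assumed AUC of 0.70 for 50 v 25, and about ±0.10 against pooled controls.

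If no group analysis is wanted, restate the aim in the Abstract (Objective), the Introduction and Principal Findings as tissue-level, and draw no conclusion about differentiating groups from the site-level AUC.

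The first option costs wording and two further AUCs from data already being collected, with a slightly less favourable precision figure to report. The second costs wording only, but gives up the group claim. Neither changes recruitment, imaging or the primary analysis. With enrolment expected to run to no later than July 2026, either can be settled before the analysis.

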## Methods

### Participants

This cross-sectional study will enroll a total of 100 participants, including 50 individuals diagnosed with plantar heel pain, along with 2 control groups. The first control group will consist of 25 individuals with insertional Achilles tendinopathy, for whom targeted myofascial treatments are not considered first-line interventions [23]. The second control group will include 25 pain-free individuals with a similar age, BMI, and sex distribution as the plantar heel pain and insertional Achilles tendinopathy groups. To ensure balanced representation, enrollment will be structured so that neither sex comprises more than 60% of each group. Eligibility and group assignment will be based on the inclusion and exclusion criteria outlined in Textbox 1. Screening for study eligibility will occur in three phases: (1) an online screening form, (2) a video visit with a physical therapist, and (3) an in-person clinical examination by a physical therapist. Individuals who provide informed consent and meet all criteria will be enrolled in this study.

Eligibility criteria.

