#### Sample Size

The target sample size of 50 individuals with plantar heel pain, 25 individuals with insertional Achilles tendinopathy, and 25 pain-free controls was chosen to provide a 95% CI half-width of 0.10 for an AUC of 0.70. This calculation assumes 5 muscle measurements for each participant, an intraclass correlation coefficient of 0.5 among them, and an overall active trigger point prevalence of 36% in individuals with plantar heel pain [10,74]. Further assuming that the 20 candidate biomarkers have AUCs uniformly distributed from 0.5 to 0.8, the study will have at least 85% power to obtain a biosignature meeting the desired AUC threshold.

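### The choice of up to 5 of 20 biomarkers is not made part of the cross-validation; done in the order written, the biosignature's AUC, sensitivity and specificity would be optimistic

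*Protocol article*

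**What the plan says.** All of this is in the protocol article.

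- **One sample (Participants).** "This cross-sectional study will enroll a total of 100 participants". No hold-out or external validation set is described.
- **Primary aim (Data Analysis).** The aim is to "examine the diagnostic performance of 20 candidate biomarkers".
- **Performance (Data Analysis).** "Five-fold cross-validation will be used to estimate predictive performance, and bootstrap resampling applied to obtain 95% CIs". Both procedures resample whole participants, which handles the five muscles measured on each person.
- **Ranking (Data Analysis).** "false discovery rates will be computed with the method of Benjamini and Hochberg to rank the biomarkers in order of diagnostic performance".
- **Selection (Data Analysis).** "Up to 5 top-performing biomarkers will be selected to constitute a single biosignature to achieve a target AUC >0.7", together with sensitivity and specificity each above 60%.
- **Exploratory models (Data Analysis).** Stepwise, Lasso, boosting and random-forest models have their AUC estimated in the same way as for the primary aim.
- **Planning assumption (Sample Size).** The AUCs of the 20 candidates are taken to be uniform between 0.5 and 0.8.

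No sentence says whether ranking and selection are repeated within each training fold or bootstrap sample.

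**The concern.** Cross-validation gives an honest estimate only of the steps that are redone without the held-out participants. The text gives each candidate a cross-validated performance, then ranks the 20, then picks up to five in order to reach a target. Followed in that order, all 100 participants' outcomes decide which biomarkers enter. Cross-validating the five-marker combination afterwards tests only the fitting of its weights, because the choice has already been tuned to the held-out data. A participant-level bootstrap of that fixed set would put its interval around the same optimistic value.

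The Benjamini-Hochberg step does not repair this. Adjusted p-values keep the order of the raw p-values apart from ties, so ranking on them is ranking on p-values. Even a cut on the false discovery rate limits how many null biomarkers enter; it does not shrink the estimated AUC of those that do.

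At stake are the three targets by which the biosignature will be read, and, through the cross-reference, the composite models of the exploratory aim.

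**Working it through.** **1. The plan's own figures.** Sample Size gives 5 muscles per participant, an intraclass correlation of 0.5, 36% trigger point prevalence in plantar heel pain, and a half-width of 0.10 at AUC 0.70.

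- Design effect: 1 + (5 − 1) × 0.5 = 3.
- Positive sites if controls have none (an assumption, since control prevalence is not given): 50 × 5 × 0.36 = 90, against 410 negative. Effective counts: m = 30, n = 136.7.
- Hanley-McNeil: Q₁ = 0.7/1.3 = 0.5385 and Q₂ = 2 × 0.49/1.7 = 0.5765. Variance = [0.21 + 29 × (0.5385 − 0.49) + 135.7 × (0.5765 − 0.49)]/(30 × 136.7) ≈ 0.00326, so the SE is 0.057 and the half-width is 1.96 × 0.057 = 0.112.
- If controls have 10% positive sites (115/385) the half-width is 0.101; if 36% applies to all 500 sites it is 0.086.

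The stated 0.10 lies inside this range. It is the precision for one AUC of 0.70 and says nothing about selection.

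**2. Simulation set-up.** 50 participants with plantar heel pain and 50 controls, 5 muscles each, intraclass correlation 0.5, prevalence 36% in plantar heel pain and 0% in controls unless stated. There are 20 normally distributed biomarkers with a shift of √2 × Φ⁻¹(AUC). The top five by AUC are combined by logistic regression, with five folds split by participant and 250 runs per scenario. Truth is the same fitted model's AUC in a large independent sample. The control prevalence, the correlation between biomarkers and the logistic combination are assumptions.

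**3. Mean AUC.** Outside means selected once on everyone; inside means reselected in each training fold. Bias is the outside estimate minus truth, from unrounded values.

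| True single AUCs | Correlation | Outside | Inside | Truth | Bias | AUC >0.7: outside / inside / truth |
|---|---|---|---|---|---|---|
| All 0.50 | 0 | 0.606 | 0.495 | 0.499 | +0.106 | 1% / 0% / 0% |
| All 0.50, controls 20% positive | 0 | 0.586 | 0.501 | 0.500 | +0.086 | 0% / 0% / 0% |
| All 0.50 | 0.5 | 0.550 | 0.499 | 0.500 | +0.051 | 1% / 0% / 0% |
| All 0.55 | 0 | 0.688 | 0.602 | 0.606 | +0.082 | 40% / 5% / 0% |
| Two at 0.65, rest 0.50 | 0 | 0.716 | 0.662 | 0.670 | +0.046 | 66% / 28% / 4% |
| Uniform 0.5–0.8 (protocol) | 0 | 0.951 | 0.938 | 0.941 | +0.010 | 100% / 100% / 100% |
| Uniform 0.5–0.8 (protocol) | 0.5 | 0.829 | 0.828 | 0.827 | +0.003 | 99% / 100% / 100% |

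The inside estimate is within 0.01 of truth throughout (−0.008 to +0.002).

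**4. Weak biomarkers, AUCs spread over 0.50–0.60.**

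- *Independent.* The outside estimate is 0.71 against a truth of 0.65, a bias of 0.06. It exceeds 0.7 in 62–64% of runs, against 13–18% with selection inside the folds, and the truth does so in 0.5%. In a separate set of runs all three targets were met in 48–56% of studies outside the folds and 13–17% inside.
- *Correlated 0.5.* The bias falls to about 0.01, and an AUC above 0.7 appears in about 2% of runs.

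**5. Hand check that the truth stays low.** For independent biomarkers with equal-variance normal distributions, the best linear combination has AUC Φ(√Σz²), with z = Φ⁻¹(AUC). Five at 0.55 give Φ(√5 × 0.1257) = Φ(0.281) = 0.61. On an even grid of 20 from 0.50 to 0.60, the best five have z of 0.199, 0.213, 0.226, 0.240 and 0.253. Then Σz² ≈ 0.258 and the AUC is Φ(0.508) ≈ 0.69. Even a perfect choice stays just under 0.70, so readings above it there are produced mainly by selection and sampling error.

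**The case against.** The strongest reply is that the text never places selection outside the folds. It names five-fold cross-validation and a bootstrap, both by participant, as the estimators of performance. It also sends the exploratory models, which have selection or tuning built into fitting, through the same procedure, so the cross-validation can be read as wrapping model building. A condensed article may leave this to an analysis plan that is not shown. That stands, and the point is therefore conditional. What remains is that the article itself sets out a sequence and a ranking device that, followed literally, give a biased primary result.

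Stronger readings are tempting but not supported:

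- *The reported performance is certainly inflated, or using the same 100 participants is itself the error.* With selection inside the folds, the estimate on those participants is close to unbiased.
- *The bias is large whatever the truth.* Under the protocol's own AUC assumption it is about 0.01. The large target-met rates need weak and mutually independent biomarkers. Independence is doubtful, because several MRI measures come from the same regions of interest.
- *Pure noise would pass.* With 20 null biomarkers an AUC above 0.7 appears in about 1% of runs or fewer.
- *There is no multiplicity control at all.* The wording allows fewer than five, so a false discovery rate cut is possible. With an assumed cut of q < 0.05, 88% of null studies select nothing. In the weak, independent case, however, the targets are still met in 35%.
- *The targets are a go/no-go rule.* The document calls them a target and presents the findings as groundwork for later studies.

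**Conclusion.** The point holds as a conditional one. The plan does not tie the choice of biomarkers to the resampling. If the written order is followed, cross-validated AUC, sensitivity and specificity are optimistic, and the Benjamini-Hochberg ranking does not remove this.

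The AUC bias is:

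- about +0.01 with AUCs uniform from 0.5 to 0.8, as the protocol assumes;
- about +0.05 to +0.11 with null or weak independent biomarkers;
- at a correlation of 0.5, about 0.01 for weak and 0.04 to 0.06 for null biomarkers.

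The worst case for interpretation is independent biomarkers with AUCs of 0.50 to 0.60, where an AUC above 0.7 appears in up to about 60% of studies although the truth almost never exceeds it. These sizes rest on the simulation assumptions listed above. The favourable case rests on biomarker strengths that the study is meant to find out, so the estimate should also be reliable if they turn out weaker.

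**What to change.** State in Data Analysis that ranking, the choice of up to five biomarkers, model fitting and cut-point choice are all repeated inside every training fold, with only held-out participants scored. Run the same full procedure in every participant-level bootstrap sample. Keep all copies of one participant in the same fold, since otherwise a duplicate can sit in both training and test data. Judge the AUC, sensitivity and specificity targets on these nested estimates only. Report Benjamini-Hochberg q-values separately, as evidence for single biomarkers. Apply the same rule to the exploratory composite models, which borrow the primary procedure.

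The cost is a few sentences and more computing time, with no change to recruitment or data collection. The nested AUC will be slightly lower and slightly conservative, because each model is trained on about 80 of the 100 participants.

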### Conclusions

This protocol provides novel mechanistic insights into myofascial pain through advanced imaging, offering a biopsychosocial framework for improved diagnosis and treatment of plantar heel pain and related conditions. We anticipate that combining imaging and psychosocial measures will improve the diagnostic accuracy of the biosignature and provide a more comprehensive understanding of myofascial pain.

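### The exploratory composite adds demographics and psychological factors together, so no planned comparison isolates the AUC gain from psychological factors

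*Protocol article*

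**What the plan says.** The question is put in terms of psychological factors throughout. The Objective in the Abstract is to "explore whether diagnostic accuracy is enhanced by creating a composite biosignature that includes psychological factors". The Introduction proposes "composite biosignatures that combine multiple imaging biomarkers with psychological factors, such as kinesiophobia". The Conclusions state: "We anticipate that combining imaging and psychosocial measures will improve the diagnostic accuracy of the biosignature". Principal Findings in the Discussion repeats that expectation, and the section on psychosocial factors asks how such factors may improve an imaging biosignature. None of these places mentions demographics.

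The composite is specified only in Statistical Analysis, Data Analysis. There, "composite biosignatures will be developed from imaging biomarkers, patient demographics, and psychological factors". On fitting: "Composite models will be built from the full set of predictors using stepwise variable selection", alongside Lasso, gradient boosting and random forests. On performance: "ROC AUC will be estimated as the measure of diagnostic performance for each model, as described for the primary aim". The section also promises variable importance and partial dependence plots, and calls the aim exploratory. It does not list which variables count as demographics. The imaging-only benchmark is the primary biosignature in the same section, made of up to 5 top-ranked biomarkers.

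**The concern.** The stated question is incremental: how much does accuracy rise when psychological factors are added? The stated analysis enters two non-imaging blocks at once and gives one AUC per model. The natural comparison, composite against primary imaging biosignature, changes three things together: demographics, psychological factors and the way the model is built. A rise in AUC could come from any of them.

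Demographics and questionnaire scores are both fixed within a participant, while the AUC is pooled over 5 muscles per participant. Both blocks can therefore separate only participants, not muscles within a participant, and they compete for the same information. A comparison that adds both cannot say which one helped.

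At stake is the support for the conclusion that the article anticipates about psychosocial measures. The primary aim and its targets (AUC >0.7, sensitivity and specificity >60%) are not affected.

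**Working it through.** The article gives no figure for the composite aim, so there is none to reproduce. The check has three parts.

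**1. The models side by side**

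| Model | Imaging | Demographics | Psychological | Built by |
|---|---|---|---|---|
| Primary biosignature | up to 5 markers | no | no | ranking of 20 candidates |
| Composite | yes | yes | yes | stepwise, Lasso, boosting, random forests |
| Reference for the psychological increment | yes | yes | no | same method as the composite: not named |

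The increment asked about is AUC(imaging + demographics + psychological) − AUC(imaging + demographics), with the method held fixed. The third row is the missing term. Variable importance does not replace it: a predictor can have non-zero importance in a fitted model and still add nothing to cross-validated AUC.

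**2. Can demographics alone produce a gain? Large-sample illustration**

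Assumptions, not from the article: independent normal predictors, imaging AUC 0.70 (separation d_I = 0.742), no psychological effect, and a demographic score with separation d_D.

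AUC = Φ(√(d_I² + d_D²) / √2)

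- Imaging alone: Φ(0.742/1.414) = Φ(0.525) = 0.700
- d_D = 0.2: √(0.551 + 0.04) = 0.768; AUC 0.707, gain 0.006
- d_D = 0.3: √(0.551 + 0.09) = 0.800; AUC 0.714, gain 0.014
- d_D = 0.5: √(0.551 + 0.25) = 0.895; AUC 0.737, gain 0.036

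So a gain is possible with psychology contributing nothing, but it is small. For scale, the Sample Size section plans a 95% CI half-width of 0.10 for a single AUC of 0.70. That is only a rough yardstick, since it is not the precision of a paired difference between two models.

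**3. Simulation at the study's size**

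From the article: 100 participants × 5 muscles and participant-level 5-fold cross-validation. Assumed: about 36% positive sites overall, imaging AUC 0.70, a participant random effect (SD 0.8), three demographics of which one is active, six psychological scores with no effect, and a ridge logistic model. There were 400 trials per setting.

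| Demographic effect per SD | Imaging | + demographics | + psychological | Full − imaging | Psychological step | Full beats imaging | Psychological step raises AUC |
|---|---|---|---|---|---|---|---|
| log-OR 0.6 (OR 1.8) | 0.691 | 0.724 | 0.710 | +0.019 | −0.014 | 81% | 11% |
| log-OR 0.4 (OR 1.5) | 0.691 | 0.703 | 0.688 | −0.003 | −0.015 | 46% | 13% |
| log-OR 0 | 0.691 | 0.682 | 0.665 | −0.026 | −0.017 | 7% | 12% |

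A separate run of the same design gave 78% and 13% at OR 1.8, 42% and 11% at OR 1.5, and 8% and 14% with no effect. The article gives 36% only for plantar heel pain, so the run was repeated at about 25% positive sites. It gave 75% and 12% at OR 1.8, and 41% and 13% at OR 1.5.

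These percentages count any positive difference. In 150 trials with a participant-level bootstrap, the 95% CI for composite minus imaging excluded zero in 17% (OR 1.8) and 2% (OR 1.5) with ridge, and in 60% and 19% with a fixed-penalty Lasso. Adding the null psychological scores cost about 0.014 to 0.018 AUC with ridge but about 0.001 or less with Lasso.

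**The case against.** **The descriptions do not contradict each other.** A composite that includes psychological factors may include other things too, and the Discussion and Conclusions state expectations, not definitions. This stands. The mismatch is between the question and the analysis that is meant to answer it.

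**Nothing says that a demographic gain will be credited to psychology.** A reader might infer this from the wording of the Conclusions, but the documents do not support it. The Data Analysis section commits to showing the contribution of each predictor, so an active demographic would be visible. This stands, although such displays do not give the AUC increment. Nor does the article say which demographics enter: sex is named for interaction tests, while age and BMI appear only as variables on which the groups are made similar.

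**Nested models may be left to a fuller plan.** The article condenses its protocol and does not rule out reduced models. This stands in part: one cannot say that the study is unable to answer its question. But the article does state both the question and the predictor set, and as stated they do not meet.

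**Demographic signal is limited by design.** The pain-free group is to be similar in age, BMI and sex, and neither sex may exceed 60% of a group. This limits the problem without removing it, because the classified outcome is tissue with or without myofascial pain, not group membership.

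**The simulated sizes rest on assumptions.** The demographic odds ratios and the null psychological effects are assumed, ridge is not a planned method, and any positive difference counts as a gain. All of this stands. The loss of AUC from useless predictors is largely a feature of ridge and should not be pressed as a second harm.

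**Conclusion.** The point holds in a limited form. The article asks about the gain from psychological factors, but its stated composite adds demographics as well and names no reference model that would separate the two. A comparison with the imaging-only biosignature would mix demographics, psychological factors and method.

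The possible size is small: about +0.02 AUC at an assumed odds ratio of 1.8 per SD. At 1.5 there is no average gain under ridge, and with no demographic effect the apparent gain disappears. How often a gain would look convincing depends heavily on the fitting method. These figures show that the ambiguity can matter; they do not predict this study's result.

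Severity is low. The aim is exploratory, and no threshold or decision attaches to the composite. The stronger reading, that a demographic gain would be reported as a psychological one, goes beyond the documents.

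**What to change.** In the exploratory part of the Data Analysis section, fit two models for each method on the same participant-level folds: (a) imaging + demographics, and (b) imaging + demographics + psychological factors. Report the paired difference in cross-validated AUC, b minus a, with a 95% CI from the participant-level bootstrap already planned for the primary aim. Base any statement about psychological factors on that difference. Mention demographics where the objective describes the composite.

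The cost is one extra fit per method and a few words of text, with no new participants or measurements. The psychological gain reported may turn out smaller than a comparison with imaging alone would suggest.
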